#### Secondary outcome

Secondary outcomes will include measurements of Interleukin-6 (IL-6), S100 calcium-binding protein β (S100β), insulin-like growth factor-1 (IGF-1), tumor necrosis factor (TNF-*α*), and C-reactive protein (CRP) both before and on the third day after the operation. These factors are significantly elevated and closely associated with POCD (45–49). S100β, present in glial and Schwann cells, increases in blood and cerebrospinal fluid with brain damage and serves as a marker for POCD (50). IL-6 is a proinflammatory cytokine involved in CNS inflammation (51). IGF-1 protects dopaminergic neurons and delays their degeneration, particularly in midbrain regions (52). TNF-*α*, a key proinflammatory cytokine, is associated with autoimmune and cognitive disorders (53). CRP, a non-specific inflammatory biomarker, accelerates neurodegenerative diseases by activating microglia and proinflammatory pathways (49). IL-6, IGF-1, TNF-α, and S100β will be quantified using commercial ELISA kits (Beyotime, China), while CRP data will be extracted from the case records.

We will also gather postoperative data, including information on exhaustion, defecation and eating times, and the time of the first postoperative ambulation. Additionally, Numeric Rating Scale (NRS) scores will be collected before and on the third day after the operation, along with Activities of Daily Living (ADL) and Braden scale scores taken before the operation and at the time of discharge from the case records.

### Data collection and management

Throughout the study, participants will be referred to by their participant numbers rather than by their names. Additionally, all relevant documents and files will be archived for a period of 5 years and will only be accessible to investigators who have signed a confidentiality agreement or to institutional or governmental auditors during the study. Data collection and management will be monitored by the Institutional Ethics Committee of Subei People’s Hospital, Jiangsu Province.

### Statistical analysis

All data will be analyzed using IBM SPSS software version 24.0. Research data following a normal distribution and expressed as x̄± SD will be analyzed using analysis of variance (ANOVA). For non-normally distributed data expressed as median (interquartile range), the Kruskal-Wallis H test will be applied. Categorical variables, presented as frequency (f) and percentages (%), will be analyzed using the chi-squared test and Fisher’s exact test as appropriate. Multiple imputation methods will be employed to handle missing data.

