**Methods:**

A total of 266 geriatric patients who underwent radical resection of gastrointestinal tumors will be divided into seven groups: one control group (receiving standardized perioperative management), one sham intervention group (receiving TEAS treatment without electrical stimulation), and five intervention groups (receiving TEAS at different time intervals). The intervention groups will receive TEAS at bilateral Neiguan (PC6) and Zusanli (ST36) acupoints. The TEAS treatment will employ an altered frequency of 2/100 Hz with disperse-dense waveforms and an adjustable intensity, ensuring the stimulation remains below 10 mA and within a tolerable range for the patient. The device will output an asymmetrical biphasic pulse wave, with a pulse width of 0.2 ms ± 30%, based on electromagnetic compatibility basic performance testing. The primary outcome will assess changes in cognition, measured using neuropsychological tests administered preoperatively and 3 days postoperatively, as well as the Telephone Interview for Cognitive Status-Modified (TICS-m) at 1, 3, and 6 months postoperatively. Secondary outcomes will include preoperative and 3-day postoperative measurements of interleukin-6 (IL-6), S100 calcium-binding protein β (S100β), tumor necrosis factor alpha (TNF-*α*), insulin-like growth factor 1 (IGF-1), and C-reactive protein (CRP). Additional data will be collected on the time to postoperative exhaust, defecation, eating, and the first postoperative ambulation. Numeric Rating Scale (NRS) scores will be recorded before and on the third day after the operation, alongside Activities of Daily Living (ADL) and Braden scale scores, which will be assessed before the operation and at the time of discharge.

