### Patient population and setting

The equation for sample size calculation, *n* = (Z*
_α/2_
* + Z*
_β_
*)^2^ × 2*σ*^2^/δ^2^ where σ represents the average score of the Mini-Mental State Examination (MMSE) evaluated on the third day after the operation between the two groups. Based on previous pre-experimental data, this study employs a two-sided test with *α* = 0.05 and a test efficiency of (1-β) = 0.9, resulting in Z_α/2_ = 1.96, Z_β_ = 1.282. *σ* denotes the standard deviation, while *δ* represents the mean difference of MMSE scores on the third day after the operation between the intervention and control groups. According to the pre-experiment results, σ is 2.35, δ is 2.0, and considering a 30% increase in the sample size, each group requires 38 patients. Therefore, a total of 266 patients will be sequentially enrolled after meeting the eligibility criteria, with the attending doctor informing each patient and obtaining their informed consent. This study adheres to the principles of the Declaration of Helsinki.

To expand our pool of research subjects, we will promote recruitment on the hospital’s official account. Throughout the intervention, patients will retain the final decision-making authority regarding their participation in the trial.

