### Outcome measures

#### Main outcome

The primary outcome of this study will be the change in cognition. The neuropsychological test will be measured preoperatively and 3 days postoperatively. Telephone Interviews for Cognitive Status-Modified (TICS-m) will be measured 1, 3, and 6 months after the operation.

The neuropsychological test includes the Mini-Mental State Examination (MMSE), Auditory Verbal Learning Test-HuaShan version (AVLT-H), Digital Symbol Coding (DSC), Verbal Fluency Test (VFT), and Clock Drawing Task (CDT). These assessments will be conducted by experienced researchers who have received training in neuropsychological assessment. Postoperative cognitive dysfunction (POCD) is defined as occurring when two or more Test *Z*-values or the *Z*-total exceed 1.96, according to the “Z-score method” (31).

The MMSE is a widely used tool for detecting cognitive impairment in both clinical and research settings (32). This 30-point questionnaire evaluates various cognitive domains, including orientation (time and place), memory (immediate and short-term), attention, calculation, and language (naming, repetition, listening, reading, and writing) (33). A higher score indicates better cognitive function.

AVLT-H has been shown to be acceptable to Mandarin speakers and is sensitive to detecting amnestic mild cognitive impairment (aMCI) (34). It assesses memory by requiring patients to learn and recall a set of 12 words. Due to the knowledge and cooperation levels of the local elderly subjects, we will record their fourth recall, with each correctly recalled word earning 1 point (35).

DSC assesses executive function. In this test, subjects are required to match numbers with corresponding symbols within 90 s. Each correctly matched number earns 1 point (36). This test is a valid and reliable measure for detecting early signs of cognitive decline (37) and predicting cognitive disorders (38).

VFT primarily assesses language ability but also requires the integration of several cognitive functions, including speed, attention, inhibition, and self-monitoring (39). Although the task is relatively simple, it reflects the effective coordination of these functions (40). In the test, subjects are instructed to name as many animals, fruits, and vegetables as they can within 1 min. Each correctly named item earns 1 point, and repeated items receive no points (41).

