## Discussion

Research has shown that the timing of TEAS interventions—whether administered 10–30 min preoperatively, throughout the entire surgical procedure, or solely preoperatively versus a combination of preoperative and postoperative treatment—can significantly improve cognitive function (12–14). Extended use of TEAS may lead to a “tolerance effect,” potentially diminishing its efficacy over time (19). Consequently, this protocol aims to investigate the optimal timing for TEAS to improve postoperative recovery in elderly patients. The results are expected to assist clinicians in formulating more effective perioperative management strategies, reducing the incidence of POCD, and enhancing postoperative cognitive function and quality of life for elderly patients.

Additionally, given the potential for a “tolerance effect” associated with prolonged TEAS use, it is essential to examine how varying intervention durations at different timings might influence this phenomenon. Future research should evaluate the impact of different intervention durations at these timings to ensure the sustained efficacy and safety of TEAS. Furthermore, exploring the effects of TEAS across diverse surgical procedures and patient subgroups will contribute to validating its generalizability and applicability. Further studies are needed to confirm the long-term effects and safety of TEAS to establish its reliability in clinical practice.

This study has several notable strengths. Firstly, it is the pioneering investigation into the effects of different TEAS timings on the postoperative recovery of elderly patients with gastrointestinal tumors, as previously mentioned. Second, we assessed the long-term cognitive function. Many studies have discussed TEAS in the short term, for example, in the third and seventh days after the operation (32, 45). However, POCD can last for months or years, and we investigated the cognitive function of patients 1, 3, and 6 months postoperative (6).

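### TICS-m, part of the primary outcome, is read three times per patient, but no method named for scores is stated to use the three readings together

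*Protocol article*

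**What the plan says.** The Main outcome section of the protocol article makes change in cognition the primary outcome and includes this: "Telephone Interviews for Cognitive Status-Modified (TICS-m) will be measured 1, 3, and 6 months after the operation". Each patient therefore contributes up to three readings of the same instrument.

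The Statistical analysis section assigns a test to each type of data. Normally distributed data "will be analyzed using analysis of variance (ANOVA). For non-normally distributed data expressed as median (interquartile range), the Kruskal-Wallis H test will be applied". Categorical data go to chi-squared or Fisher's exact test, and missing data to multiple imputation. The section does not say which form of ANOVA is meant. It mentions no patient, visit or arm-by-visit term. It does not say whether the TICS-m visits are tested separately or together, and it makes no TICS-m time point the main one.

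The Discussion counts the long follow-up among the strengths of the study: "we investigated the cognitive function of patients 1, 3, and 6 months postoperative".

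The sample size rests on day-3 MMSE, not on TICS-m: "this study employs a two-sided test with *α* = 0.05 and a test efficiency of (1-β) = 0.9", and "σ is 2.35, δ is 2.0, and considering a 30% increase in the sample size, each group requires 38 patients". The article gives no SD and no within-patient correlation for TICS-m.

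**The concern.** The article is not silent on method. It gives a rule for scores, and that rule does not fit an outcome read three times on the same patient. Kruskal-Wallis compares independent groups with one value per subject. It cannot use three readings unless they are first reduced to one summary, and none is named. The same holds for one-way ANOVA, the form that normally has Kruskal-Wallis as its fallback.

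The likely result is one seven-arm test at each of 1, 3 and 6 months, with three consequences:

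- Part of the primary outcome gets three chances to be significant, with no stated correction and no visit designated in advance.
- No test compares the arms over the whole follow-up, so the persistence that the Discussion stresses is read from three separate p-values.
- Each test ignores the patient's two other readings. This matters most for small differences, and differences between timings of an active treatment may well be smaller than the intervention-versus-control difference behind the sample size.

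**Working it through.** **1. The plan's own figure.** From Patient population and setting: two-sided α = 0.05, power 0.90, σ = 2.35, δ = 2.0, 30% increase.

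n = (1.96 + 1.282)² × 2 × 2.35² / 2.0² = 10.51 × 11.045 / 4 = 29.02. Then 29.02 × 1.3 = 37.7, rounded up to 38, and 7 × 38 = 266. The stated sample size is reproduced. The standardised effect is 2.0 / 2.35 = 0.85.

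**2. Which named test TICS-m scores would meet.** Normal scores go to an ANOVA of unstated form, non-normal scores to Kruskal-Wallis. The non-normal route is realistic, because TICS-m is capped at 50 points and patients with preoperative cognitive dysfunction are excluded. On that route there is no joint use of the visits under any reading of the word ANOVA.

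**3. Three separate tests: false positives.** If the three tests were independent, the chance of at least one false positive would be 1 − 0.95³ = 0.143. The readings are correlated, so this was simulated: 7 arms × 38 patients × 3 visits, no true difference, equal correlation ρ between visits, 8,000 trials per value of ρ. The values of ρ are assumptions.

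| ρ | each visit's test | at least one of three | test on patient's three-visit mean |
|---|---|---|---|
| 0.3 | 4.9% | 13.6% | 4.7% |
| 0.5 | 5.1% | 13.3% | 5.0% |
| 0.7 | 5.2% | 11.8% | 5.0% |

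**4. Precision.** With equal variances, the mean of three visits has variance (1 + 2ρ)/3 times that of one visit: 0.667 at ρ = 0.5 and 0.867 at ρ = 0.8. Write s for its square root (0.816 and 0.931), with s = 1 for a single visit. With complete data, the visit-averaged arm difference from the mixed model is the difference in these patient means. For a standardised difference d that is constant over visits, pairwise power at two-sided 5% is Φ(d × √(n/2) / s − 1.96).

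For example, with n = 38 and d = 0.5, one visit gives Φ(0.5 × 4.359 − 1.96) = Φ(0.22) = 0.59. The three-visit mean at ρ = 0.5 gives Φ(2.179 / 0.816 − 1.96) = Φ(0.71) = 0.76.

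| n per arm | d | one visit | three-visit mean, ρ = 0.8 to 0.5 |
|---|---|---|---|
| 38 | 0.85 | 0.96 | 0.98 to 0.995 |
| 38 | 0.5 | 0.59 | 0.65 to 0.76 |
| 30 | 0.85 | 0.91 | 0.94 to 0.98 |
| 30 | 0.5 | 0.49 | 0.55 to 0.66 |

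The rows with 30 per arm show roughly what remains if the whole 30% allowance is lost (38 / 1.3 = 29.2). The value d = 0.85 is carried over from day-3 MMSE, and d = 0.5 is an assumption.

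**5. Illustration only: visits pooled as independent rows.** Seven arms × 38 × 3 = 798 rows in one ANOVA would give false-positive rates of about 25%, 39% and 52% at ρ = 0.3, 0.5 and 0.7. Kruskal-Wallis is within about 3 points of these. The plan does not propose this analysis.

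**The case against.** The strongest reply has four parts.

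- **Unqualified ANOVA may include repeated-measures ANOVA, and a condensed article leaves model terms to the full protocol or analysis plan.** This stands in part. The pairing with Kruskal-Wallis makes the one-way form likely but does not prove it, and the absence of a covariance structure or contrast is not a fault in an article. What remains is the stated rule, which sends non-normal TICS-m scores to a test that takes one value per patient.
- **One test per visit is valid, and its power loss is trivial at the plan's effect.** Both statements are right: each test holds 5%, and 0.96 against 0.98–0.995 is a small difference. The loss is material only for smaller differences. The 12–14% figure matters if significance at any one visit would be taken as a positive long-term finding, and the article does not exclude that.
- **Visit-by-visit tests answer a legitimate question.** They do, and an average dilutes an effect that fades. The visit-specific estimates should therefore stay, as description.
- **TICS-m may be reported as impairment categories.** The article gives cut-offs (below 28 for dementia, 28–32 for mild impairment) and, in its limitations, describes the scale as detecting impairment. The chi-squared or Fisher rule would then apply and a linear model would not fit. This stands, and the fix allows for it. The difficulty is the same, since those tests also treat observations as independent.

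A reader might also infer that the plan inflates the false-positive rate to 25–52%. The documents do not support that. No passage pools visits as independent patients, and the range depends on an assumed correlation of 0.3–0.7.

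**Conclusion.** The point holds as a cheap improvement. Three correlated TICS-m readings per patient belong to the primary outcome. The methods named for scores state no joint use of them, and Kruskal-Wallis cannot provide it.

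On the likely reading each visit's test is valid. The cost is three uncorrected looks (about 12–14% for at least one false positive, ρ 0.7–0.3), no comparison over the whole follow-up, and lower precision. The precision loss is slight at the plan's effect and moderate at 0.5 SD.

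These sizes rest on assumed correlations, equal variances and, for power, an effect constant over visits and a standardised effect borrowed from another instrument on day 3. The point does not show that the planned analysis is invalid, and it does not affect the day-3 tests or the stated sample size.

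**What to change.** For TICS-m scores, replace the ANOVA/Kruskal-Wallis rule with one linear mixed model:

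- Fixed effects for arm, visit (1, 3 and 6 months) and arm-by-visit, with an unstructured within-patient covariance.
- The arm effect averaged over the three visits as the single main long-term comparison.
- The visit-specific arm estimates, with confidence intervals, as the description of persistence.
- A statement that readings from different visits are not entered as independent observations.

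If TICS-m is reported as impairment categories, use a repeated-measures logistic model (GEE) in the same way. Keep the one-way tests for outcomes with a single postoperative reading.

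The cost is one or two sentences. The MIXED procedure in the SPSS version already named fits the linear model, and no new patients or data are needed. The downside is that the averaged effect is less sensitive to a difference present at one visit only. The change settles the three visits only; multiplicity across the seven arms and across the day-3 tests is a separate matter.

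### The named ANOVA and Kruskal-Wallis tests do not adjust for the preoperative values collected for most continuous outcomes, and it is not stated whether day-3 or change scores are compared

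*Protocol article*

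**What the plan says.** Three parts of the protocol article bear on this point.

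- **Main outcome.** "The primary outcome of this study will be the change in cognition". The battery (MMSE, AVLT-H, DSC, VFT, CDT) is given before surgery and again on day 3. TICS-m is given only at 1, 3 and 6 months.
- **Patient population and setting.** The effect used for sizing is "the mean difference of MMSE scores on the third day after the operation between the intervention and control groups". The figures are "σ is 2.35, δ is 2.0, and considering a 30% increase in the sample size, each group requires 38 patients".
- **Statistical analysis.** Normally distributed data "will be analyzed using analysis of variance (ANOVA"), skewed data go to Kruskal-Wallis, and categorical data go to chi-squared or Fisher tests. Missing values are multiply imputed. No covariate, ANCOVA, regression or repeated-measures model is named in the article.

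Under Secondary outcome, the five biomarkers and NRS have a value before surgery and one on day 3, and ADL and Braden have one before surgery and one at discharge. The times to flatus, defecation, eating and first ambulation have no baseline by their nature.

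**The concern.** A patient's preoperative score usually predicts part of the postoperative score. When that score is already in the data set, using it as a covariate removes predictable variation at almost no cost. The tests named in the article do not do this, and Kruskal-Wallis cannot.

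The article also leaves open what is compared. If ANOVA is run on day-3 scores, the preoperative value is not used. If it is run on change scores, the preoperative value is subtracted in full, which over-corrects when the correlation is below 1, and the relevant SD need no longer be the 2.35 used for sizing.

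The trial aims to find the best timing among five active schedules, so differences between arms of 38 matter. Chance differences at baseline then affect the observed ordering of arms, either through the day-3 scores or, with opposite sign, through the change scores.

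**Working it through.** **Inputs from the article:** two-sided α = 0.05 (z = 1.96), power 0.90 (z = 1.282), SD 2.35, difference 2.0 MMSE points, 30% increase, seven groups.

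**Assumptions:** the correlation ρ between preoperative and day-3 scores is not given, so one common range of 0.3, 0.5 and 0.7 is used throughout. The preoperative SD is taken to equal the day-3 SD.

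**Step 1: reproduce the plan's figure.** n = (1.96 + 1.282)² × 2 × 2.35² / 2.0² = 29.02. Then 29.02 × 1.30 = 37.7, rounded up to 38 per group, and 38 × 7 = 266. Both stated figures reproduce. They rest on day-3 scores with no baseline term.

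**Step 2: variance relative to a day-3 analysis.** Day-3 scores: 1. Change scores: 2(1 − ρ). ANCOVA: 1 − ρ². Because 1 − ρ² = (1 − ρ)(1 + ρ) and 1 + ρ is at most 2, ANCOVA never exceeds the change-score value. It also never exceeds 1. The cost of estimating one slope is ignored.

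**Step 3: pairwise power for 2.0 points.** Power = Φ(2.0 / (SD × √(2/n)) − 1.96), with n = 30 (29.02 rounded up) and SD equal to 2.35 times the square root of the variance factor. For day-3 scores: 2.0 / (2.35 × √(2/30)) = 3.296, and Φ(3.296 − 1.96) = 90.9%.

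| ρ (assumed) | Variance: change | Variance: ANCOVA | Power: day-3 | Power: change | Power: ANCOVA |
|---|---|---|---|---|---|
| 0.3 | 1.40 | 0.91 | 90.9% | 79.6% | 93.3% |
| 0.5 | 1.00 | 0.75 | 90.9% | 90.9% | 96.8% |
| 0.7 | 0.60 | 0.51 | 90.9% | 98.9% | 99.6% |

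Equivalently, ANCOVA would need 27, 22 and 15 patients per group before the 30% increase, against 30 for the day-3 analysis.

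As an illustration only, at α/6 (six groups each against control, a rule the article does not state) power goes from 74.5% with day-3 scores to 79.3%, 87.9% and 97.6% with ANCOVA.

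**Step 4: chance imbalance.** The standard error of a baseline difference between two groups of 38 is 2.35 × √(2/38) = 0.54 points, so the 95% range is about ±1.06. An imbalance of one standard error shifts the comparison as follows:

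- Day-3 scores, ρ × 0.54: 0.16, 0.27 and 0.38 points at ρ = 0.3, 0.5 and 0.7.
- Change scores, (ρ − 1) × 0.54: −0.38, −0.27 and −0.16 points.
- ANCOVA removes this shift, up to the error in estimating the slope.

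**The case against.** The strongest reply is that a short analysis section in a journal article need not list covariates, and that an analysis plan not shown may add them. It is also true that unadjusted ANOVA in a randomised trial is valid, and that its standard error already allows for chance imbalance. All of that stands, and it limits the point to efficiency. It does not remove the point, because the article names its tests, and a more precise test is available on data it already collects.

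Four stronger readings are tempting but not supported:

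- **That every main measure has an unused baseline.** TICS-m is part of the primary outcome and has no preoperative value. The Discussion acknowledges that before-and-after comparison is not possible for it. The recovery times have none either.
- **That the baseline is certainly ignored.** The primary outcome is worded as change, so ANOVA may be meant for change scores. The POCD classification, which uses Z-values from a battery given before and after surgery, may also use the baseline. The article does not settle this.
- **That imbalance passes in full into the ranking.** In a day-3 comparison it enters multiplied by ρ. A one-standard-error imbalance moves the comparison by 0.16 to 0.38 points, against a 2.0-point target.
- **That the gain is always large, or that change scores always lose power.** At ρ = 0.3 the ANCOVA gain is about two percentage points. At ρ = 0.7 change scores do better than day-3 scores. A low ρ is plausible here, because eligibility excludes preoperative cognitive dysfunction and requires more than five years of education, and MMSE is capped at 30.

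**Conclusion.** The point holds as a recommended improvement. Preoperative values exist for the day-3 battery, biomarkers, NRS, ADL and Braden. The tests named do not adjust for them, and the article does not reconcile an outcome of change with sizing on day-3 scores.

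Over ρ from 0.3 to 0.7, ANCOVA reduces variance by 9% to 49% relative to day-3 scores, and is at least as precise as change scores at any ρ. At the planned effect and the unadjusted 5% level, power is already about 91% on day-3 scores, so the gain there is modest. It is larger at a stricter significance level. The choice matters most if change scores are analysed and ρ is low: at 0.3, power would be about 80%, below the planned 90%.

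A reader might infer that the treatment estimates will be biased. The documents do not support that: with randomisation working as intended, both unadjusted analyses are unbiased on average. The figures rest on the assumed ρ, on equal SDs before and after surgery, and on a normal approximation. The direction for ANCOVA does not depend on the value of ρ.

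**What to change.** State in the Statistical analysis section that each continuous day-3 or discharge outcome with a preoperative value is analysed by ANCOVA on arm plus that outcome's own preoperative value. Use a transformed or rank-based version where the distribution is skewed. This also settles the day-3 versus change question: with the preoperative value as a covariate, the two give the same arm differences.

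For TICS-m, adjust for preoperative MMSE or the preoperative battery score, since it has no baseline of its own.

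The covariate should be a value taken before the first TEAS session, which in some arms falls on the day before surgery.

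The cost is analysis wording and one degree of freedom per model. No new data and no change to the sample size are needed.
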